### Data collection

Online questionnaires assessing demographics (e.g., age, gender), primary outcomes (i.e., prosocial behavior, intrinsic prosocial motivation, social competence, social autonomy, and social relatedness) and secondary outcomes (i.e., school wellbeing, social position, and antisocial behavior) will be completed by children prior to the start (T1) of the program. Halfway through the program (T2) and after completion of the program in the intervention condition (T3), children complete questionnaires about program content (i.e., working elements) in addition to questionnaires assessing primary and secondary outcomes. Teachers complete questionnaires about demographics (e.g., age, years of experience), attitudes, and civic skills at T1 and questionnaires about attitudes, civic skills, program content (to assess program integrity), and program evaluation at T2 and T3. Additionally, one teacher from each school will participate in the focus groups (at T1, T2, and T3), to evaluate the implementation of the program (i.e., qualitative information). Table 1 presents an overview of the instruments at each assessment point.

**Table 1 Tab1:** Overview of the variables’ instruments and sources

Outcome	Variable name	Instrument	Time of measurement	Variable type	Source
Primary outcomes					
Prosocial behavior	Injunctive norm	Developed for this study	T1, T2, T3	Outcome	Child
	Prosocial behavior (individual)	Based on the Strengths and Difficulties questionnaire (SDQ), subscale prosocial behavior	T1, T2, T3	Outcome	Child
	Prosocial behavior (according to classmates)	Sociometric nominations	T1, T2, T3	Outcome	Child
	Cooperation in the classroom	Classroom Peer Context Questionnaire (CPCQ), subscale cooperation	T1, T2, T3	Outcome	Child
	Conflict in the classroom	Classroom Peer Context Questionnaire (CPCQ), subscale conflict	T1, T2, T3	Outcome	Child
Intrinsic (prosocial) motivation	Social goals	Developed for this study	T1, T2, T3	Outcome	Child
Social competence	Self-esteem	Developed for this study, based on de Rosenberg Self-Esteem Scale	T1, T2, T3	Outcome	Child
Social autonomy	Social autonomy and responsibility	Developed for this study, based on the School as a Caring Community Profile – II and Child Development Project [34]	T1, T2, T3	Outcome	Child
Social relatedness	Comfort and cohesion	Classroom Peer Context Questionnaire (CPCQ), subscale comfort and cohesion	T1, T2, T3	Outcome	Child
Secondary outcomes					

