### Study sample

We aim to include *N* = 42 schools to ensure there is enough power for the analyses (*N* = 21 schools for both the intervention and waitlist control condition). This sample size is sufficient to examine the effectiveness of Meaningful Roles and potential moderators, with a power of 0.80, an alpha of 0.05 and a medium effect size of 0.21 [18].

Participants are children from the upper grades of primary school (grades 5–8) in the Netherlands, their teachers (who will implement the program) and school leaders. The children will mostly be between 8 and 12 years old.

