#### Teacher focus groups

In addition to the questionnaires, focus groups for teachers will be organized at T1, T2, and T3 to evaluate the implementation of Meaningful Roles. One delegate teacher per school will be asked to participate in these focus groups. Delegates can talk about their experiences with the intervention program and research, and are encouraged to make suggestions about important questions that should be included in the data collection waves for teachers and school leaders (at T2 or T3), in order to understand how feasible the implementation has been and what should be improved about the program. Semi-structured interviews will be used for the focus groups. The purpose of these focus groups is thus threefold: 1) information can be used as an indicator of the process evaluation (qualitative research information as an addition to the questionnaires) to understand strengths and difficulties in the execution of the intervention and evaluation of the research. This information can also help to understand why stronger or weaker effects may be found in different schools (i.e., interpretation of effects); 2) information can be used to give suggestions for improving the program in the future; and 3) information can be used to add any questions to the intermediate measurement (T2) and final measurement (T3) that, in the experience of the teachers, seem important to measure regarding the implementation (not the outcomes). These findings are used to clarify the findings in the context of the implementation process.

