### Statistical analyses

Before the analyses, possible baseline (T1) differences in demographics and outcome variables (baseline assessment) between children in the intervention program and the control condition will be checked with ANOVA (continuous variables) and chi-square analyses (categorical variables). To investigate the effectiveness of the intervention program, regression analyses will be performed. The dependent variables are the outcome measures at intermediate (T2) or posttest (T3), condition is the predictor variable (1 = intervention, 0 = control), and baseline (T1), potential differences between the experimental and control group at T1, or intermediate measures (when dependent variables are the outcome measures at T2) are the covariates. The effect of potential moderators (categorial or continuous) on the outcomes will be examined by adding interaction effects to the models.

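### The covariate rule for the effectiveness regressions includes mid-program (T2) measures: as printed the T2 model is degenerate, and under the other plausible readings it adjusts for a post-randomisation variable

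*Protocol article*

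**What the plan says.** All of this comes from the protocol article.

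- **Purpose of the model** (Statistical analyses): "To investigate the effectiveness of the intervention program, regression analyses will be performed". No mediation question or T2-to-T3 change question is declared there.
- **Outcomes and predictor** (same section): "The dependent variables are the outcome measures at intermediate (T2) or posttest (T3), condition is the predictor variable (1 = intervention, 0 = control". This sentence itself ties the word intermediate to T2.
- **Covariates** (same sentence): T1 values, T1 differences between the groups, "or intermediate measures (when dependent variables are the outcome measures at T2) are the covariates". Moderator interactions are then added to these models.
- **Timing** (Data collection): the first questionnaires "will be completed by children prior to the start (T1) of the program". The later two waves are placed as follows: "Halfway through the program (T2) and after completion of the program in the intervention condition (T3".
- **Same usage elsewhere** (Teacher focus groups): "information can be used to add any questions to the intermediate measurement (T2) and final measurement (T3".
- **Design effect size** (Study sample): the trial is planned "with a power of 0.80, an alpha of 0.05 and a medium effect size of 0.21", with 21 "schools for both the intervention and waitlist control condition".

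**The concern.** Schools are randomised to start at once or a school year later, so every T2 value in the intervention arm is measured after randomisation and under exposure to the program. A model meant to estimate what the program does should not condition on something the program may already have changed. The covariate rule does so in every model that uses the intermediate measure, and no other section corrects it.

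Two things are at stake. First, the printed rule for T2 outcomes cannot be applied in any meaningful way, so the T2 analysis is in effect unspecified. Second, the most natural repair, reading T3 where T2 is printed, does not give a sound effectiveness model. It gives one whose condition coefficient leaves out benefit that had already arisen by mid-program and carried through to T3. Because moderator terms are added to the same models, the moderator results would be affected too.

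**Working it through.** **The plan's own figure.** The only design figure is 42 schools for an effect of 0.21. It cannot be reproduced, because the article gives neither the number of children per school nor an intraclass correlation. Without clustering, the two-sided requirement is 356 children per arm, or 712/42 ≈ 17 per school. This does not bear on the present point. The value 0.21 is used below only as a plausible T3 effect, taken to be in standard deviation units.

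**Reading 1, as printed: T2 outcome adjusted for the T2 measure.** The regression is Y2 = a + b·condition + c·Y1 + e·Y2. Least squares solves it exactly with e = 1 and a = b = c = 0. In one simulated data set of 712 children with a true T2 effect of 0.21, the condition coefficient was 0 and the Y2 coefficient 1. With T1 as the only covariate, the same data gave 0.284, which is 0.21 plus sampling error.

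**Reading 2, T3 meant: T3 outcome adjusted for T1 and T2.** Let d2 and d3 be the program effects at T2 and T3, with no group difference at T1. Let b2 be the slope of T3 on T2 given T1. The condition coefficient is then

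d3 − b2·d2,

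and the share removed is b2·f, where f = d2/d3.

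With unit variances, b2 follows from the within-child correlation r:

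- Equal correlation between all waves: b2 = (r − r²)/(1 − r²). For r = 0.6 this is 0.24/0.64 = 0.375.
- First-order autoregressive: b2 = (r − r³)/(1 − r²) = r. For r = 0.6 this is 0.6.

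The values of r, the correlation structure and f are all assumptions, because the article gives none of them. With d3 = 0.21:

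| Structure | r | b2 | f | d3 − b2·d2 | Removed |
|---|---|---|---|---|---|
| Equal | 0.4 | 0.286 | 0.50 | 0.180 | 14% |
| Equal | 0.6 | 0.375 | 0.50 | 0.171 | 19% |
| Equal | 0.6 | 0.375 | 0.75 | 0.151 | 28% |
| Equal | 0.6 | 0.375 | 1.00 | 0.131 | 38% |
| Equal | 0.7 | 0.412 | 1.00 | 0.124 | 41% |
| Autoregressive | 0.6 | 0.600 | 0.75 | 0.116 | 45% |
| Autoregressive | 0.7 | 0.700 | 1.00 | 0.063 | 70% |

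Over r from 0.4 to 0.7, both structures and f from 0.5 to 1, the loss runs from 14% to 70%. If T2 replaces T1 instead of joining it, the coefficient is d3 − r·d2. That runs from 0.168 (20% removed) to 0.063 (70% removed).

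**Reading 3, T2 values of other variables.** The Current study section expects the program to raise autonomy, competence and relatedness, and through them motivation and prosocial climate. Adjusting a T2 outcome for T2 values of those components removes whatever part of the effect runs through them. The article gives nothing from which to size this.

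**The case against.** The strongest reply is that the clause, as printed, belongs to T2 outcomes only. Taken at its word, T3 outcomes are adjusted for T1, and the T3 effect is untouched. The list is also joined by the word or, which allows models with T1 covariates alone. **This stands.** A reader might infer that the main T3 result is certainly biased, but the text does not establish that. The shrinkage applies only if T3 was meant, and only in the models that use the intermediate measure.

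A second reply is that nobody would report a regression of a variable on itself as evidence that the program does not work. The perfect fit would show at the first run. **This stands too.** The printed version is a drafting error that leaves the T2 model undefined, and it is not a credible route to a false negative result.

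Third, the shrinkage needs T2 to predict T3 and a T2 effect of the same sign as the T3 effect. With no T2 effect, the expression returns d3 unchanged. **Also right**, so a bias towards zero is conditional.

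Fourth, a reader might want a figure for lost power. None can be supported. Power under T2 adjustment depends heavily on how school and class effects correlate across waves, and the article does not say.

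Two further replies do not succeed. A T2-to-T3 change or mediation analysis would be a legitimate use of T2, but the section presents these regressions as the test of effectiveness and declares no such question. Nor is this detail left to a fuller analysis plan: the article states the covariate rule itself.

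**Conclusion.** The point holds in a limited form. The stated covariate rule is wrong for an effectiveness analysis under each of the three readings: degenerate as printed, and adjusted for a post-randomisation variable if T3 or other T2 variables were meant. In the latter two cases, the models using that covariate do not estimate the total program effect.

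For the T3 reading, about 14 to 70% of the effect is removed over the assumed range, for example 0.21 to between 0.13 and 0.17 with equal correlations of 0.6. These sizes are illustrations. They rest on assumed within-child correlations, an assumed correlation structure and an assumed T2 effect of 50 to 100% of the T3 effect. The direction rests on less: T2 predicts T3, and the two effects share a sign. The documents do not support the claims that the T3 analysis is biased as written, that the program would be reported as ineffective, or that power falls by a given amount.

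**What to change.** Delete the clause on intermediate measures. State that outcomes at T2 and at T3 are each adjusted for the T1 value of that outcome and other pre-randomisation covariates only. If the team wants a T3 model that includes T2, declare it separately as an exploratory analysis, and say whether its target is T2-to-T3 change or mediation.

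The cost is one sentence in Statistical analyses, plus one more if the exploratory analysis is kept. No new data are needed, and the measurement schedule does not change.

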### Current study

In sum, the current protocol describes a study that will be conducted to examine the effectiveness of a classroom-based program promoting a prosocial classroom climate (i.e., Meaningful Roles). Figure 1 presents the conceptual model of the research design. A cluster RCT will be performed to investigate if the program results in more prosocial classrooms (e.g., more prosocial behavior, more cooperation, less conflict). The program will be compared to a control condition. We will use a multi-informant (children, teachers, and school leaders) and multi-method (questionnaires and focus groups) design. As illustrated in Fig. 1, it is expected that Meaningful Roles will increase children’s social autonomy, social competence, and social relatedness, resulting in an increase in intrinsic (prosocial) motivation and a prosocial classroom climate (i.e., increased prosocial behavior, positive teacher attitudes, civic skills, and school wellbeing, and reduced bullying and bullying victimization). In addition, the second aim is to examine moderators of effectiveness. This is important because it is likely that Meaningful Roles is not equally effective across child, teacher, school, and program characteristics (i.e., program integrity). The final aims of this study are to evaluate the working elements of Meaningful Roles (i.e., meaningful roles, classroom meetings, and compliments) and to evaluate how the program is experienced by teachers and school leaders.

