#### Moderators

*Child, teacher, and school characteristics* will be collected at baseline. Child characteristics include age, gender, romantic attraction (i.e., possibility of falling in love with a boy/girl), grade, and ethnic identity. Teacher characteristics include age, gender, years of experience (as a teacher in general, and as a teacher at the specific school) and experience with implementing social safety programs, as well as attitudes of the teachers. School characteristics include location, number of participating grades and students in the classrooms, and years of experience with a social safety program (e.g., KiVa).

*Working elements* will be assessed halfway through the program (T2) and after completion of the program (T3), with specific questions developed for this study. Children and teachers fill in questionnaires related to the three main components of the program: 1) meaningful roles (e.g., “How much did you like the role(s)”, “Which roles were the most popular?”, respectively), 2) classroom meetings (e.g., “The weekly meetings were done independently by the class”, “How often has a meeting been held?”, respectively), and 3) compliments (e.g., “I have received compliments from my classmates”, “How many times a week has attention been paid to the compliments?”, respectively). Higher scores reflect a more positive or greater adherence of the working elements.

*Program integrity* will be assessed halfway through the program and after completion of the program, with specific questions developed for this study. Teachers and school leaders fill in (open and closed) questionnaires related to the implementation of the program, divided into the domains training and material (e.g., “How often have you used the manual?”), child questionnaires (e.g., “Where there any questions that the children struggled with?”), time investment (e.g., “How did you feel about the time you had to implement the program properly?”), and global impression (e.g., “What is your general impression of the degree of success of the implementation of the program?”). Higher scores reflect a more positive or greater adherence of the program.

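### One power 0.80 / alpha 0.05 statement is made to cover both the main effect and the moderators, but neither figure carries over to the moderator aim

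*Protocol article*

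**What the plan says.** Moderation is a formal aim. Under Current study the article writes: "In addition, the second aim is to examine moderators of effectiveness", and it expects the program's effect to differ across child, teacher, school and program characteristics.

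Under Study sample, after setting 42 schools (21 per arm), it writes: "This sample size is sufficient to examine the effectiveness of Meaningful Roles and potential moderators, with a power of 0.80, an alpha of 0.05". The target is "a medium effect size of 0.21". No ICC, number of children per school or size of interaction is given, and no moderator is named.

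Under Instruments, Moderators, the characteristics collected at baseline can be counted:
- **Child (5):** age, gender, romantic attraction, grade, ethnic identity.
- **Teacher (6):** age, gender, years of teaching, years at the school, experience with social safety programs, attitudes.
- **School (4):** "School characteristics include location, number of participating grades and students in the classrooms, and years of experience with a social safety program".

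That makes 15. Working elements and program integrity, measured after randomisation, come on top.

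Under Statistical analyses, outcomes are modelled at T2 or T3, and for moderators: "The effect of potential moderators (categorial or continuous) on the outcomes will be examined by adding interaction effects to the models". No moderator, outcome or time point is put first.

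**The concern.** The sample-size sentence puts the moderator aim on the same inferential footing as the main effect, with the same power and the same alpha. Two things follow for a reader who takes it at face value.

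First, a null interaction would be read as evidence that the program works equally well everywhere, because the trial was said to have 80% power. If real power is far lower, that reading is unsafe.

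Second, a nominally significant interaction would be read as holding at 5% error, although it may be one of many examined. Such a result could steer which schools or teachers are advised to use the program.

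**Working it through.** **Inputs from the article.** Alpha 0.05, power 0.80, effect size 0.21, 21 schools per arm (Study sample); 15 baseline characteristics (Moderators); 9 primary variables (Table 1); 2 analysed time points (Statistical analyses). **Assumed:** two-sided testing, 0.21 as a standardised mean difference (SD 1), no baseline adjustment, and every correlation below.

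**1. The plan's own figure.** Before clustering, n per arm = 2(1.960 + 0.842)² / 0.21² = 356 children. With m children per school, 21 schools per arm give exactly 80% power when 21m / [1 + (m − 1)ICC] = 356. Solving for the ICC gives 0.009 at m = 20, 0.035 at m = 40, 0.043 at m = 60, 0.047 at m = 80 and 0.049 at m = 100. Since m and the ICC are not given, 42 schools can be neither confirmed nor refuted. The next steps therefore grant the article its 80% for the main effect.

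**2. School-level moderator, split 50/50.** Let V be the variance of a school mean.
- Main effect, two groups of 21: variance = 2V/21 = 4V/42.
- Interaction, a difference of differences over four cells averaging 10.5 schools: variance = 4V/10.5 = 16V/42.

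The variance is four times as large, so the standard error doubles. A main effect with 80% power has expected z = 1.960 + 0.842 = 2.80. An interaction of the same size has z = 1.40, and power = Φ(1.40 − 1.96) = Φ(−0.56) = 0.29. To reach 80%, the interaction would have to be twice as large: 2 × 0.21 = 0.42.

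**3. Child-level moderator, split 50/50 within every school.** School effects cancel in the within-school contrast. If the interaction itself does not vary between schools, the ratio of interaction variance to main-effect variance is 4(1 − ICC) / [1 + (m − 1)ICC]. At the pairs from step 1:

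| m | ICC | variance ratio | z = 2.80/√ratio | power |
|---|---|---|---|---|
| 20 | 0.009 | 3.36 | 1.53 | 0.33 |
| 40 | 0.035 | 1.64 | 2.19 | 0.59 |
| 60 | 0.043 | 1.08 | 2.69 | 0.77 |
| 80 | 0.047 | 0.81 | 3.12 | 0.88 |
| 100 | 0.049 | 0.64 | 3.49 | 0.94 |

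So, for an interaction of 0.21, power can lie well below or somewhat above 0.80, depending on the level of the moderator and on m and the ICC.

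**4. Error rate over the moderator list.** Suppose there is no true moderation and each of 15 interactions is read at 0.05, for one outcome at one time point.
- Independent tests: 1 − 0.95¹⁵ = 0.54; expected false positives 15 × 0.05 = 0.75.
- Equally correlated tests: 0.46 at correlation 0.3, 0.41 at 0.4 and 0.36 at 0.5.

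**5. If more outcomes were crossed (the article does not say so).**
- Five primary domains, one time point: 15 × 5 = 75 tests, 3.75 false positives expected. The chance of at least one is 98% if independent, and 82% to 97% in simulation with moderator-test correlation 0 to 0.4 and outcome correlation 0.3 to 0.7.
- Nine primary variables, two time points: 15 × 9 × 2 = 270 tests, 13.5 false positives expected. The chance of at least one is about 95% to nearly 100% over all correlations tried (moderator tests 0 to 0.5, outcomes 0.2 to 0.8, time points 0.5 or 0.6).

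The expected counts do not depend on the correlations.

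**The case against.** The strongest reply is that this is a condensed article with a one-paragraph statistics section. Moderator ranking, a multiplicity rule and exploratory labels commonly sit in a statistical analysis plan, which is not shown. That stands: their absence here is not an error in itself.

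A reader might infer that the trial will test all 15 moderators on every outcome at an unadjusted 0.05, so that a false subgroup claim is almost certain. The article does not support this:
- Statistical analyses speaks of the outcomes in general. It states neither full crossing nor a decision rule for each interaction, and the 0.05 appears only in the sample-size statement.
- The 15 items are characteristics to be collected. Table 1 labels child and teacher demographics as moderator or covariate, so some may serve only for adjustment.
- The wording is partly tentative. Moderators are called potential, and the Discussion says only that a large, diverse sample might make their study possible.
- The Background gives prior evidence or reasoning for most of the list, including child age, gender and ethnicity, teacher experience, class size and location.
- A nominally significant interaction becomes a false claim only if it is reported as established.

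The correlations in steps 4 and 5 are also assumptions. Some pairs, such as age with grade, may be more strongly related than 0.5, which would lower the risk.

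What the reply does not reach is the positive claim under Study sample. An analysis plan can add a multiplicity rule, but it cannot make one power figure correct for both a main effect and a school-level interaction.

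**Conclusion.** The point holds in a limited form. The statement that 42 schools give power 0.80 at alpha 0.05 for effectiveness and for potential moderators is not supported as written.

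- **Power:** about 29% for a balanced school-level moderator with an interaction as large as the main effect, granting 80% for the main effect. An unbalanced split would do worse. Child-level moderators may do better or reach the target, but this depends on an ICC and a cluster size that the article does not state.
- **Alpha:** 0.05 would not describe the moderator aim as a whole. At 36% to 54%, the risk for one outcome at one time point is about 7 to 11 times the stated 0.05. This assumes that all 15 interactions are read at 0.05, that there is no true moderation, and that test correlations lie between 0 and 0.5. Testing more outcomes and both time points raises it.

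A near-certain false claim is not established, because it requires a crossing and a decision rule that the article does not state.

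**What to change.** Under Study sample, restrict the power and alpha statement to the main effect and take moderators out of it. Under Statistical analyses, add that moderator analyses are exploratory and will be reported as interaction estimates with 95% confidence intervals, without claims of significance.

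If the team wants some confirmatory moderator claims, it can name a short list, tie it to one primary measure at one time point, and control the error over the list with Holm's method. This is optional, and the content of the list is for the team to choose. Any power stated for it should be computed for the interaction itself, at the level at which the moderator varies.

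The cost is a few sentences, with no extra data or schools. The downside is that moderator results can no longer be presented as established; on a Holm-controlled list, each test also becomes somewhat stricter.
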